### 12.3.6 Generation of Follow-up Lists

At each visit and for each community the study coordinator will be responsible for supplying the field team with a census book to update the census with new household members, permanent

moves out of the village and deaths that occurred in the previous six months. The census book will be generated by clicking the appropriate bottom under the reports menu of the access data base.

Once the data entry for the census update has been completed, the computer will select at random the sentinel children to be examined, and the ocular forms and corresponding labels for the selected children will be printed. If the visit includes annual treatment, treatment forms for each household will be also generated.

### 12.3.7 Periodic Reports

Reports will be issued for each visit with summary information on key variables. In order to explore problems with standardization, the reports will be stratified by community, and by interviewer/examiner. If any irregularities are detected, investigators will be informed and re-standardization of pertinent procedures will take place.

Participant tracking reports will be generated for each visit. These reports will be given to the project manager, who will determine whether the visits have been conducted. If the visits were not conducted, he/she will work with the field team so that a follow-up visit can be scheduled. If the visit was conducted, but no data have yet been entered into the data system, he will make sure that the data for that visit is entered.

Periodic reports for quality assurance will also be prepared. These include the following: Trachoma grading: The Coordinating Center will receive the grades from [name] on the ocular photographs for each grader at each visit. These will be compared to the clinical grades given to the same children. Agreement will be determined, using the kappa statistic, for TF and TI. A report is generated on the agreement to the Study site investigator and to the Executive Committee. If agreement is below kappa 0.6, then the Study Site investigator will responsible for carrying out re-standardization exercises as described in Chapter 17.

Field Laboratory specimen reports: the Coordinating Center is responsible for receiving the data on the positivity of the air field specimens, and generating a report on the rate of positivity by visit and by lab technician. A report is generated to the Study Site Investigator and to the Executive Committee. If field contamination is greater than 1%, then remedial actions in the field are required to bring the field operations back to standard, as discussed in Chapter 17.

### 12.3.8 Data Storage

At the office in Kongwa, data will be stored in locked file cabinets. Electronic databases in Kongwa will be backed up to an external drive on a daily basis and periodical backups will be stored off-site. At the Dana Center, for the analysis phase, the data will be transferred into a Sun station UNIX base system, where SAS permanent data files will be created. Three generations of backup files are kept at all times for this computer. One copy is housed off-site. In the central computer, tape backups are performed daily. Four tapes are used during the week (labeled Monday-Thursday). There are four Friday tapes (Friday1 to Friday 4) for each Friday of the month. At the end of every week (Friday), backups are done on the weekly tapes. There are twelve monthly tapes (January to December). At the end of each month, the backup is done on the monthly tape. This procedure ensures the possibility of retrieval of old versions of files up to one year old.

To maintain data and study documentation, codebooks with question-by-question specification of all questionnaire responses will be created and updated periodically. Furthermore, a complete description of all data files will be kept. This description will include the file creation date, the number of records, the record layout, the field names and description and a list of allowable codes for each field.

### **12.3.9 Preparation of data for transfer to LSHTM, UCSF**

Once the data for a single visit for all the communities has been entered and edited, SAS permanent data sets will be created. These data sets will be used for all the statistical analysis and the generation of official reports. Customized programs will be used to extract the information required for the analysis to be carried out both in San Francisco and London. The de-identified data and corresponding documentation will be sent electronically using the data transfer protocol described in the previous section. Persons are only identified using a study number.

## **12.4 The Gambia**

### **12.4.1 Study Forms Preparation**

#### **12.4.1.1 CENSUS FORMS**

At baseline, each census taker is given a set of forms for a census enumeration area (CEA), and a list of household numbers unique to them, developed by prior listing of household heads. Census enumeration areas have unique 'geocodes' in the 2003 Gambian census which are five digit numbers. The household numbers may begin with a unique letter, then sequential numbers. At subsequent census, a master Census book is created with the most recent version of the census for that CEA, which is used to update the census with new arrivals and departures.

#### **12.4.1.2 MASTER SURVEY LIST**

The Master Survey List is a copy of the original census document. In the 3 'longitudinal' CEAs all children 0-9 are chosen, and in the 9 'sample CEAs 100 children aged 0-5 are randomly selected, together with 10 reserves. The registration form then contains the full spelling of each individual's name, as well as their age, gender, and household number. A new randomized Master Survey List is generated for each CEA at each collection visit and is used for both mobilization (the day before collection is scheduled) and registration.

#### **12.4.1.3 OCULAR EXAMINATION FORM**

The Examination Form is printed for each of the children who will be part of the sample survey in each CEA. Labels are also pre-printed for placing on sample tubes, photo log books, and specimen shipping log books.

#### **12.4.1.4 BLANK CENSUS UPDATE FORMS**

Blank forms are brought each day to the field during surveys or mass treatment in case they are needed to update information on sample children or residents.

## **12.4.2 Daily Data Management Activities in Field**

All completed Master Survey Lists, Census update forms, Ocular Examination Forms and, depending on the activity, mass Treatment or Census books will be given to the Study Coordinator at the end of each workday and stored in a safe, secure place for transport to Fajara. The Study Coordinator will check the forms for completeness and accuracy.

## **12.4.3 Data Entry**

The treatment data collected in the field will be entered into a database at The Sheikh Zayed Regional Eye Care Centre by National Eye care Program staff. A double entry on key fields, using the uniform Access data entry package created for each site, will be done to minimize data entry errors. The study coordinator will do the final editing. The collection fieldwork data will be entered into a database by The Gambia's Database Manager, who will also oversee the work of the staff member helping to double-enter the data. The Gambia Database Manager will also enter all PCR results into the database.

## **12.4.4 Preparation of Data for Transfer to LSHTM**

### **12.4.4.1 DATA MANAGEMENT**

All treatment and collection data will be entered within four working weeks of collection. Data will be entered and inconsistencies will be resolved by the respective study coordinator or, if necessary, by consultation with the appropriate data collector. Access to any patient information will be protected by a password, or locked in a secure storage room. All data will be backed up upon entry, and forms will be kept until the conclusion of the study.

### **12.4.4.2 RECONCILIATION OF DATA**

Before data entry, the forms will be reviewed and cross-checked for consistency and completeness. If the forms are not filled out completely, the Study Coordinator will contact the person responsible for completing the form to provide missing data or clarify any inconsistent data. The Study Coordinator is the only person who is authorized to add missing data or make any changes to the study forms. All changes will be made in a different color ink and initialed and dated.

### **12.4.4.3 SPECIMEN TRANSFER PROCEDURES**

In accordance with the Roche COBAS AMPLICOR™ CT/NG protocol, swab samples taken in the field will be transported on ice in a closed, insulated container to Fajara, where they will be stored at -80°C for analysis on site. Where sample aliquots need to be sent outside the Gambia for QC or further analysis they will be imported into the USA as per the CDC Permit to Import/Transfer Etiological Agents or Vectors of Human Disease, and into the UK as per COSSH

(Control of substances hazardous to health) guidelines. Locally stipulated regulations for the transfer of samples from MRC The Gambia will be fully met.

#### **12.4.4.4 PREPARATION OF DATA FOR TRANSFER TO UCSF**

Once the data for a single visit for all the communities has been entered and edited, SAS permanent data sets will be created. These data sets will be used for all the statistical analysis and the generation of official reports. Customized programs will be used to extract the information required for the analysis to be carried out both in San Francisco and London. The de-identified data and corresponding documentation will be sent electronically using the data transfer protocol described in the previous section. Persons are only identified using a study number.

## Chapter 13: Quality Assurance Policies and Procedures

---

### 13.1 Overview

Several policies and procedures are built into this project in each country in order to provide assurances of quality in the data collection, processing, and management, as well as assuring proper treatment of all participants. General QA procedures include:

- Intensive training sessions: All individuals involved in the study will undergo training and certification for all study procedures for which they are responsible. Training and certification procedures are described in chapter 11.
- Development of standardized forms and procedures for completion of forms. This includes procedures for recovery of missing data and changing responses, if necessary, as described below.
- Monthly data editing, report generation, and reconciliation, with feedback to the clinical sites in The Gambia, Niger, and Tanzania, and the laboratories by each Data Coordinating Center. These procedures are described extensively in each Chapter, and in Chapter 12. The process of providing periodic feedback on missing data or incomplete or out of range data is critical to timely recovery, identification of problems, and remedial actions to ensure that problems are solved.
- Monitoring of quality of trachoma grading and laboratory procedures used in the field, and in the laboratory. The Data Coordinating Centers will review the adherence to randomization procedures, treatment administered, timely follow-up of villages on schedule, agreement among graders for trachoma assessment in collaboration with [name], and laboratory evidence of contamination of specimen collection or inadequate specimens. If the review uncovers a problem, the CC will notify the Study Site Principal Investigator, as well as issue reports to the Executive Committee. The clinical sites will immediately institute retraining procedures, including suspending a staff member from performance of the task until adequate performance can be demonstrated.
- Within each clinical site, the project directors have planned bi-weekly meetings of the census, survey, treatment, and the Data Entry Teams, to review reports and study progress, and address problems identified by the Data Coordinating Center.
- Masking of survey team as much as possible, and certainly the laboratory personnel, to treatment randomization. This procedure avoids bias in detection of infection, and determination of outcome.
- Active oversight by the Project Director in the field at the commencement of each study visit. The project directors will ensure the next phase of each part of the project proceeds smoothly, the data flow is steady, and the feedback for the new phase is in place.

- Site Monitoring with 6 monthly site visits by the Study Site Principal Investigator. These will focus on adherence to protocols, review of team meetings, and resolution of any issues.
- Creation of a paper or electronic trail to any data modifications and limiting access to the main database. Extensive back up procedures that protect the quality of the database. These procedures help ensure the integrity of the database.
- The Executive Committee will meet every six months to monitor, across sites, study progress, address any issues arising from data quality monitoring, review safety reports and review consent procedures.

## 13.2 General Guidelines for Form Completion

A significant component of quality assurance for data collection is the proper completion of forms. Detailed instructions for the completion of each form are provided in chapter 10, so this section is intended to provide guidelines for the completion of all forms. The following rules apply when completing the forms:

- Complete forms in “real time”. Do not fill in the forms at a later time, or more convenient time. Later completion has a high potential for recall bias, missing data, or wrong data. The form must be filled in while the child/family member is present. The most difficult form to accomplish this will be the mass treatment form, which may be completed over a period of days for the village. However, it is essential that all persons be accounted for in terms of treatment. In the event of missing data, the staff must NOT try to recall the missing treatment but re-question the family to capture the data. If this cannot be done, it is better to code the data as missing (see below).
- Use only black ink for initial forms completion
- Use only red ink for alterations/edits to original entries on forms, which must be initialed by the person making the change.
- Check to make sure that ID labels/data and **study** identifiers are on every page of every form. Forms that do not have this information are to be referred back to the study site project directors for clarification and review.
- **Print all written responses**
- Do not change units or re-phrase questions.
- Enter data in the units and number of digits prescribed on form. Do not record fractions. Use a decimal only if it is written on the form. Be sure to include a value behind a decimal point, if applicable.
- Right justify all numbers, entering leading and following zeroes where applicable.
- Left justify all letter codes, leave remaining spaces blank.
- Write pertinent comments in the margins or on the last page of the form.
- Review all responses for completeness; skip patterns and accuracy before signing off on a form.

## 13.3 Missing Data on Study Forms

Missing forms or specimens are discussed in Chapter 12. In summary, procedures conclude with the person responsible signing off on missing items or forms or vials that all attempts to locate have been undertaken and the item is missing. This form is transmitted to the Coordinating Centers in order to update the Master File.

If some data within forms are missing and cannot be obtained when the form is reviewed, then an appropriate code is inserted in the empty data field to indicate missing or not applicable.

### **13.4 Changing Responses on Study Forms**

In general, responses should not be changed unless there was a transcription error or the discovery of incorrect data by one staff on a form prepared by another. In these cases, the following guidelines should be adhered to:

Preserve the audit trail, so changes can be traced from original response to the changed response. Often, this means nothing more than making corrections on the original form. In the case of responding to questions raised by the data entry clerks, be certain that the missing data/specimen forms are properly filled out and accounting made to site project directors.

Do not obliterate, erase or white-out incorrect response. To correct a response: draw 1 or 2 lines through incorrect response, write correct response next to or about it in red ink, put initials and date in the margin by the correction.

### **13.5 Oversight**

The Project Directors at each site will be responsible for overseeing the initiation of all phases of data collection. Thus, together with the study site principal investigators, the project directors will be present at the start of each new phase of data collection, specifically the census, surveys, mass treatment, and new rounds of each. The Project Director will be responsible for ensuring that each type of visit runs smoothly, and will remain onsite until all individuals involved in data collection for that visit type are comfortable with the data collection procedures. They will also be certain that the Data Entry team follows the procedures for each type of data entry, is operating smoothly, and responsibly storing the forms.

Bi-weekly staff meetings of project staff during census, survey, and will be held to review progress in enrollment/follow-up, review outstanding problems with forms or data entry, and reconcile reports from the coordinating center. The staff can report field problems, issues in dealing with the villages, and other concerns that might arise. All staff can attend, including drivers.

### **13.6 Adherence to Procedures**

The Data Coordinating Center for each clinical site will monitor adherence to the procedures for randomization, mass treatment administered, census and follow-up surveys, adherence to standards for trachoma grading and laboratory evidence of contamination of specimen collection or inadequate specimens. Mechanisms are in place to ensure that villages are randomized to each treatment group in the absence of bias by study staff; and the treatment assignment is not known to the laboratory personnel.

### **13.7 Quality Assurance for Field Trachoma Grading**

The images taken will be organized into folders for each examiner by visit. The folders will be sent to [name] for review and grading, as he is the standard to which all the field graders have been trained. He will grade each set of 50 digital images for quality of the image, using 2.5 magnification. The first observation is for grade-ability of the image. If more than 20% of the images are ungradeable for any one photographer, the clinical site will be notified, certification of photographer will be suspended and the photographer will have to be re-certified.

[name] will grade each gradable photograph with a clinical grade for trachoma, using the WHO simplified grading scheme. The grades will be transmitted to each study site data coordinating center, which will compare the grades with the grades assigned to the eyes in the field. Agreement will be assessed, and if agreement falls below 0.6 in any month, the reasons for disagreement will be discussed, and the set of photographs re-circulated to bring agreement to acceptable levels. If necessary, the survey will be interrupted while the study site lead investigator and the field grader re-grade photographs and undertake field work until agreement is re-established. Some of the disagreement could be due to differences between grading photographs and grading live eyes in the field, although we have shown very high concordance.

The quality assurance of grading in the field is a required report from each center that will be presented at six months to the executive committee for review and reported to the DSMC during their annual review.

### 13.8 Quality Assurance for Specimens

Once per year, a set of five positive and five negative specimens from each laboratory will be re-aliquoted and half the sample will be sent to [name] laboratory, masked as to the findings from the original lab. [name] lab will re-run the results, as will the lab of origin for confirmation of results, thus providing assurances of similar procedures across laboratories. There must be at least 80% concordance of results between the laboratory and [name] lab.

The following steps will be followed:

- [name] and the lab of origin will send their results to the study site CC.
- The CC will send a report of the concordance, with ID numbers of non-concordant results, to the lab of origin and to [name].
- If concordance is at least 80%, the CC will issue a one year quality assurance certificate to the lab and to [name] for his records, and to the Executive committee.
  - If concordance is less, the CC will issue a provisional notice to the lab chief and [name], who must work together to resolve the difference, including re-sending specimens until concordance is reached. Once concordance is reached, the quality assurance certificate is again issued to the lab and to [name] for his records, and to the Executive Committee. Note that some of the discrepancy may be due to issues with shipping, resulting in loss of positivity of specimens. To the extent possible the re-aliquoted specimens in the laboratory will be stored under conditions that mimic the shipping and re-storage so that conditions of the specimens are similar.

The Executive Committee will review yearly the quality assurance certificates for the laboratories. Data on continued quality assurance will be presented to the DSMC.

There is also the possibility of field contamination, which is checked by using the “blue air” specimens. Each laboratory will process these controls masked as to their status as controls. The CC for each site is responsible for reporting the positivity of the negative field controls to the study site investigators. If the rate is above 1%, then the investigators must take remedial action to correct field procedures to remove contamination. Data on field contamination results will be presented to the DSMC for each site by the CC.

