## 7.2.4 Laboratory Processing Procedures

A dry swab is taken in the field, a study identification label is affixed, and the vial is kept frozen until it reaches each country team's designated laboratory as described above. The specimens are processed according to strict protocol, outlined in the manufacturer's kit directions, followed by the Johns Hopkins International Chlamydia Laboratory, the Molecular Biology Laboratory at the University of California at San Francisco, and the laboratory at the medical Research Council in The Gambia. We will use the Roche Amplicor *C. trachomatis* qualitative PCR assay from Roche Molecular Systems. Procedures are summarized as follows: Each swab is eluted by vortexing in Amplicor CT/NG lysis buffer in polypropylene tubes, and then Amplicor specimen diluent is added. Using a known positive sample in the laboratory, we will create positive and negative *C. trachomatis* (CT) processing controls; two CT+ and two CT- processing controls are run with each batch of specimens. The Working master mix is created and the specimens prepared prior to amplification. The specimens and controls are placed in the thermal cycler for amplification. Once completed, the specimens are denatured, and sent for detection using probe-coated microwell plates. Detection is accomplished by measuring the optical density at  $A_{450}$ . The assay result for the negative controls should be less than 0.2  $A_{450}$ , and the assay result for the positive controls should be 0.8 or greater for ocular specimens for a valid run. We will test separately for amplification of both the target plasmid DNA and the master-mix internal control samples to determine if PCR was inhibited. Samples whose values in valid runs are  $\geq 0.8 A_{450}$  are counted as positive, and samples less than 0.2  $A_{450}$  are negative. Samples for which the result are equivocal ( $\geq 0.2$ ,  $< 0.8$ ) will be tested again; if equivocal twice, they are left as equivocal and called not positive in the analyses as no run equaled 0.8 or greater.

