#### 12.2.4.3 SPECIMEN TRANSFER PROCEDURES

In accordance with the Roche COBAS AMPLICOR™ CT/NG protocol, swab samples taken in the field will be transported on ice in a closed, insulated container until arrival in San Francisco, where they will be stored at -80°C for later analysis. Samples will be imported in the USA as per the CDC Permit to Import/Transfer Etiological Agents or Vectors of Human Disease.

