#### 17.5.1.3 THE UNIVERSITY OF CALIFORNIA SAN FRANCISCO

[name] and the UCSF CC have responsibility for the following:

- Maintenance of data entry programs for Nigerien sites

- Coordinate with JHU CC to implement study forms and data entry programs
- Training program on laboratory procedures at Standardization Workshop
- Primary responsibility for Report on Laboratory quality assurance
  - Conduct periodic testing of duplicate specimens from each laboratory for ongoing quality assurance, and feedback grades to CC at each site.
  - Create report on quality assurance of laboratory specimens for PRET executive committee with recommendations
- Create randomization scheme for STUs, and for children within STUs, monitor adherence to randomization
- Monitor adherence to yearly versus 6 monthly treatment s
- Create and maintain database for Nigerien data for the study
- Monitor receipt of data from Nigerien field office after each census, examination survey, and mass treatment
- Analyze and provide data when requested by co-investigators, and for DSMC meetings
- Appropriately back-up all data
- Develop and run data cleaning checks and quality assurance steps as part of data management; communicate with the Nigerien field site to resolve data problems
- Monitor receipt of specimens at Chlamydia Laboratory, work with Nigerien field office to account for any missing specimens, receive data on specimen results from the laboratory, and integrate into the data base
- Provide data from Niger on timely basis to LSHTM for cost effectiveness component
- Create reports on Niger data as required for progress reports on data quality assurance
- Conduct objective of creating models for trachoma elimination
- Ensure partners involvement in model data analyses and publications

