### 17.5.3 Laboratory Quality Assurance Center

[name] at UCSF has primary responsibility for reviewing the consistency of each of the laboratories in this study for determining evidence of infection using Amplicor. The directors of each laboratory, [name], [name], and [name], will have responsibility for maintaining the quality control for their laboratories, and submitting specimens once per year for quality assurance purposes. The quality control procedures are as follows:

- Within each laboratory, standard quality assurance procedures are followed, that permit each laboratory to maintain their CLIA certification, and allow the CDC to grant permission to import specimens from overseas.
- Each test run for determining positivity contains a *C. trachomatis* (+) control and a *C. trachomatis* (-) control is included in each test run of the COBAS AMPLICOR™ CT/NG. To test the effect of sample processing, a known positive sample is processed and tested in each test run. (This control is helpful when testing large numbers of negative samples.). An internal control intended to identify specimens that contain polymerase inhibitor is run routinely on each sample. The internal control helps identify false negative results.
- Once per year, a set of five positive and five negative specimens from each laboratory will be re-aliquoted and half the sample will be sent to [name] laboratory, masked as to the findings from the original lab. [name] lab will re-run the results, as will the lab of origin for confirmation of results, thus providing assurances of similar procedures across laboratories. There must be at least 80% concordance of results between the laboratory and [name] lab. The following steps will be followed:
  - [name] and the lab of origin will send their results to the study site CC.
  - The CC will send a report of the concordance, with ID numbers of non-concordant results, to the lab of origin and to [name].

- If concordance is at least 80%, the CC will issue a one year quality assurance certificate to the lab and to [name] for his records, and to the Executive committee.

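### Niger swabs are tested at UCSF and re-tested at UCSF, so the yearly between-laboratory check never takes Niger results to another institution

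*Protocol*

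**What the plan says.** Protocol 13.8, repeated in 17.5.3, sets up a yearly concordance check on ten specimens per laboratory, five of them positive and five negative. After re-aliquoting, "half the sample will be sent to [name] laboratory, masked as to the findings from the original lab". The laboratory of origin also re-runs its specimens. Both sets of results go to the coordinating center of the study site, which issues a one-year certificate if concordance is at least 80%. The stated aim is to show that procedures are alike in the different laboratories.

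The name of the reference laboratory is removed from the text, but two places identify its institution. Section 17.5.3 says that the role holder "at UCSF has primary responsibility for reviewing the consistency of each of the laboratories in this study". Section 17.5.1.3 lists among the duties of the UCSF center: "Conduct periodic testing of duplicate specimens from each laboratory for ongoing quality assurance, and feedback grades to CC at each site".

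UCSF is also a routine testing site. Section 7.2.4 names three laboratories that process study swabs: one at Johns Hopkins, "the Molecular Biology Laboratory at the University of California at San Francisco", and one at the Medical Research Council in The Gambia. Section 12.2.4.3 keeps Niger swabs on ice "until arrival in San Francisco, where they will be stored at -80°C for later analysis". Section 12.2.9 has the PCR results double-entered at Proctor, which section 2.1 places at UCSF. Section 17.5.1.3 makes UCSF the coordinating center for Niger and the author of the laboratory quality report.

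**The concern.** A between-laboratory check is informative when the two results come from laboratories that do not share a fault. For Niger, the laboratory of origin, the reference, the center that compares the results and the author of the quality report are all at UCSF. Masking the re-test to the first result prevents copying. It does not expose a fault that both UCSF runs share, and nobody outside UCSF signs the certificate.

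Infection by PCR is the outcome on which the Niger hypotheses are sized (section 4.4.1). Section 8.7 leans on it because survey teams in Niger may learn the treatment status from families. Section 17.1 presents comparison across countries as the strength of the partnership, and a fault confined to one country's laboratory would be confounded with country in that comparison.

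**Working it through.** **1. Who checks whom.** Sections 7.2.4, 12.2.4.3, 13.8, 17.5.1 and 17.5.3 set side by side:

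| Site | Laboratory of origin | Reference | Center that compares and certifies |
|---|---|---|---|
| Tanzania | Johns Hopkins | UCSF | Johns Hopkins |
| The Gambia | MRC The Gambia | UCSF | LSHTM |
| Niger | UCSF | UCSF | UCSF |

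No section sends Niger specimens to another institution for confirmation. Niger has 48 of 48 + 32 + 48 = 128 communities, or 37.5%.

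**2. What an outside re-test of the Niger set could detect.** Inputs from 13.8: five called positives, five called negatives, and an 80% limit, so three or more discordant results out of ten is a failure. I take each specimen to be split, with one part sent out. The error rates are assumptions.

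*False positives.* Assume that UCSF calls 2% of uninfected swabs positive, misses none, and that the outside laboratory does not reproduce the false result. At true prevalence p, the false share of called positives is q = 0.02(1 − p) / [p + 0.02(1 − p)], and the chance of failure is P(Binomial(5, q) ≥ 3).
- p = 1%: q = 0.0198/0.0298 = 0.664, failure 79%.
- p = 2%: q = 0.0196/0.0396 = 0.495, failure 49%.
- p = 10%: q = 0.018/0.118 = 0.153, failure about 3%.

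Section 4.4.1 projects three-year prevalences of about 1% (biannual) and 10% (annual) in Niger, and about 2% and 13% by coverage, so the low values are relevant.

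*Lost sensitivity.* Assume 70% sensitivity and p = 10%. The infected share of called negatives is 0.03/(0.03 + 0.90) = 0.032, and P(Binomial(5, 0.032) ≥ 3) is about 0.03%. Called positives carry no information on missed infections, so the re-test is almost blind here.

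**3. What the existing checks already detect.** Suppose that the UCSF reference and routine laboratories are one, with 70% sensitivity and independent misses. UCSF then fails against one partner's five positives with probability P(Binomial(5, 0.3) ≥ 3) = 16.3%. Against at least one of Johns Hopkins and the MRC this is 1 − (1 − 0.163)² = 30% per year, and 1 − (1 − 0.163)⁶ = 66% over three years. For contamination at 2%, the 50 blue air swabs of one technician in one survey include at least one positive with probability 1 − 0.98⁵⁰ = 64%. Over seven surveys (350 swabs) this is 1 − 0.98³⁵⁰ = 99.9%.

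**The case against.** The best counter-argument is that concordance works in both directions. When UCSF re-runs Johns Hopkins and MRC specimens masked, UCSF is tested too, and discordant results go to both laboratories for resolution. Step 3 shows that this finds lost sensitivity far better than an outside re-test of Niger specimens would. Each run also carries positive, negative and internal controls, and the blue air swabs pass through the laboratory masked as to their status. All of this stands, but two limits remain. The indirect check reaches Niger results only if the reference and routine laboratories at UCSF are the same or share the fault. Discordance with a partner also leads to a notice on that partner's certificate, not on Niger's.

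A reader might go further and infer three things that the documents do not support.
- **That UCSF has no outside check.** The masked re-runs of two outside laboratories contradict this.
- **That Niger is checked by the very same laboratory.** The text shows the same institution. It does not say whether the reference and the routine laboratory are one or two.
- **That a faulty assay would cost Niger much of its power.** The protocol's own case (12 per arm, difference 6 points, SD 5 points, two-sided 5%) reproduces at 80.2%, against its stated figure of greater than 80%. At 70% sensitivity the difference becomes 4.2, but if the SD scales too it becomes 3.5. The ratio stays at 1.2 and power stays at 80.2%. If part of the SD is binomial sampling (assumed prevalence 5% to 10%, 50 to 100 children), power is 68% to 77%. A large loss appears only if the SD is held at 5, which does not fit the scenario.

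The laboratory is also masked to arm (section 8.7), and primary analyses are within countries (section 1.3), so a fault would not be expected to favor an arm.

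**Conclusion.** The point holds in a limited form. Niger-origin results are never re-tested or certified by another institution, so for that site the check in 13.8 and 17.5.3 cannot deliver the between-laboratory assurance it is meant to give. This rests on 17.5.3 and 17.5.1.3 for the location of the reference, since the name in 13.8 is removed. It does not depend on whether UCSF has one laboratory or two. No actual fault at UCSF is alleged.

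The practical gain from closing the gap is modest: certification by an independent center, and better detection of false positives when prevalence is low (a 49% to 79% chance of failing the limit at 1% to 2% prevalence, under the assumed 2% rate). That gain applies to false positives that repeat at UCSF but not elsewhere. A sporadic one would probably also fail to repeat at UCSF, and contamination already in the swab would travel with the aliquot. For lost sensitivity the gain is close to nil, and the existing Johns Hopkins and MRC pairs do that work.

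**What to change.** In 13.8 and 17.5.3, state that the yearly five positive and five negative aliquots from UCSF (Niger) go, masked to the UCSF result, to another study laboratory. Johns Hopkins is the natural choice because section 7.2.4 already has it running the same Amplicor assay. A coordinating center other than UCSF, such as the one at Johns Hopkins, should compare the results and issue the certificate, and 17.5.1.3 should be aligned with this. Keep UCSF as the reference for Tanzania and The Gambia, because those pairs also test UCSF.

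The cost is one small domestic shipment and about ten assays a year moved to Johns Hopkins, plus the wording changes. No new laboratory or assay is needed.
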